Side effects	Headache, dizziness, nausea, and drowsiness, determined daily by physical examination by the intensivist, and withdrawal symptoms upon discontinuation evaluated after the drugs are stopped.

NREM, None rapid eye movement; SWS, Slow wave sleep; REM, Rapid eye movement; PSG, Polysomnography; RCSQ, Richards Campbell sleep questionnaire; VAS-A, Visual analogue scale-anxiety; CAM-ICU, The confusion assessment method for the intensive care unit.

The primary outcome will be to determine the effect of melatonin administration on the 24-hour sleep-wake cycle and subjective sleep quality, including night/day sleep time, total sleep time(TST), percentages of NREM stage 1/2, slow wave sleep(SWS) and REM, the incidence of arousals per hour, the duration of sleep without waking and the number of sleep periods.

The secondary outcomes will be: (a) objective sleep quality as assessed by the Richards Campbell Sleep Questionnaire (RCSQ); (b) anxiety levels measured using the Visual Analogue Scale-Anxiety (VAS-A); (c) stress levels via measuring the plasma melatonin, cortisone and norepinephrine; (d) levels of oxidative stress; (e) levels of inflammation; (f) the number of delirium-free days in 8 and 28 days; (g) the number of ventilator-free days in 28 days; (h) the number of antibiotic-free days in 8 and 28 days; (i) ICU length of stay; (j) overall ICU mortality at 28 days; (k) the incidence and severity of melatonin side effects in ICU patients.

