### Study setting and population

The study setting is the comprehensive ICU, Fuxing Hospital, Capital Medical University, Beijing, China. All patients admitted to our ICU with acute respiratory failure requiring mechanical ventilation and tracheotomy to assist weaning are screened daily for study eligibility.

Inclusion criteria are: (a) age ≥18-years-old; (b) Glasgow Coma Scale (GCS) score ≥10; (c) sedation with propofol, morphine, alfentanil and dexmedetomidine has been discontinued for a minimum of 36 hours (48 hours for lorazepam and midazolam); (d) expected mechanical ventilation days ≥5 days; (e) patients are clinically and biologically stable and pass the weaning screening and are therefore ready to be weaned from mechanical ventilation.

Exclusion criteria are: (a) pregnant or breast-feeding women; (b) preadmission treatment of sleep disturbances; (c) a history of convulsions, psychiatric or neurological disease, sleep apnoea, deafness or blindness; (d) alcohol consumption ≥50 units per week or drug use; (e) liver insufficiency (child-Pugh class C); (f) renal insufficiency (requires dialysis); (g) severe heart failure (the New York Heart Association classification III/IV); (h) intestinal obstruction, ileus, gastroparesis or other conditions likely to affect the enteral absorption of melatonin; (i) the use of drugs that might alter melatonin secretion and decrease plasma levels of melatonin, such as benzodiazepines, NSAIDs, corticosteroids, beta-blockers, haloperidol and amiodarone
[42, 43]; (j) known allergy to melatonin; (k) readmitted to the ICU after randomization to the study; (l) enrolled in another trial.

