**A bedside flowchart for pain management in ICU patients.**
^1^Consider the patient not cooperative if: RASS < -2/CAM-ICU+/communication or linguistic barriers. ^2^Verbal Numeric Rating (VNR) 0 = no pain, 10 = maximal conceivable pain. Ask:“Can you quantify your pain between 0 and 10?”. Consider at rest and breakthrough pain (e.g. = coughing, tracheo-bronchial aspiration). ^3^Consider the evaluation as reliable if it takes into account the subjective parameters the patients uses to evaluate their pain: cultural, religious and familial aspects, expectation for secondary benefits. ^4^Behavioral Pain Scale (BPS) 0 = absence of pain, 12 = maximal pain. -Facial expression: 1. Relaxed/2. Partially tightened/3. Fully tightened/ 4. Grimacing. -Upper limbs: 1. No movement/2. Partially bent/3. Fully bent with finger flexion/4. Permanently retracted. -Compliance to ventilation: 1. Toleration movement/ 2. Coughing but tolerating ventilation for most of the time/ 3. Fighting ventilator/4. Unable to control ventilation.

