The subjective sleep quality refers to the subjective feelings of the nightly sleep status of the patients. The baseline nightly sleep perceptive quality (day 1 9:00 pm to day 2 7:00 am) will be evaluated using the RCSQ at 9:00 am on day 2. The RCSQ contains five 100 mm visual analogue scales (VAS): sleep depth, latency, awakenings, time awake and quality of sleep (higher scores indicate better sleep). The RCSQ was pilot tested in a medical ICU and validated with overnight PSG in medical ICU patients. In our study, patients who are unable to write were assisted; the patients used their current communication strategy to indicate where the investigator should mark the VAS.

Anxiety is defined as a state marked by apprehension, agitation, increased motor activity, arousal, and fearful withdrawal. The baseline anxiety levels are assessed on day 2 at 9:00 am via self-report using the 100 mm VAS-A, which is presented to patients with a vertical orientation such as a thermometer. The bottom of the scale is the statement ‘not anxious at all’ and the top is “most anxious ever.” Patients indicate their current level of anxiety in response to ‘How are you feeling today?’. The VAS-A score is the number of millimetres from the bottom edge of the line (not anxious at all) to the patient’s mark. The VAS-A and the Spielberger State Anxiety Inventory are correlated (r = 0.4916 to r = 0.8219), demonstrating concurrent validity.

During the intervention period (days 2 to 5), outcome-related data, such as the objective and subjective sleep quality, and the anxiety level should be recorded. Analyses are limited to the fourth day (day 5 at 9:00 pm to day 6 at 9:00 am) because the potential chronophypnotic benefits of melatonin are not immediate and may take at least three days to be realised. Therefore, objective sleep quality should be monitored for one 24-hour period using the PSG from day 5 at 9:00 pm to day 6 at 9:00 pm, and the associated parameters and methods as described in the ‘Methods/Design’ section. Meanwhile, the subjective sleep quality and anxiety levels should be evaluated at 9:00 am on day 6 and the related methods have been previously described. In addition, daily information including the vital signs and lab parameters, the SOFA score, neurological monitoring (RASS, CAM-ICU, and GCS), as well as the mode, parameter and duration of mechanical ventilation should be recorded.

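### Headache, dizziness and nausea are to be determined by physical examination in tracheotomised patients, so the side-effect outcome will probably under-count them in both arms.

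*Protocol article*

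**What the plan says.** Table 1 of the protocol article defines the side-effect outcome and names its method: "Headache, dizziness, nausea, and drowsiness, determined daily by physical examination by the intensivist". The same row adds withdrawal symptoms after the drug is stopped. The list of secondary outcomes below the table calls item (k) "the incidence and severity of melatonin side effects in ICU patients".

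Under 'Study setting and population', the patients screened are those "requiring mechanical ventilation and tracheotomy to assist weaning". They must also have a "Glasgow Coma Scale (GCS) score ≥10" and have been off sedation for at least 36 hours (48 hours for lorazepam and midazolam).

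The article takes other subjective states from the patients themselves. For the sleep questionnaire, 'Data collection and management' says "patients who are unable to write were assisted; the patients used their current communication strategy to indicate where the investigator should mark the VAS". The anxiety score is obtained "via self-report using the 100 mm VAS-A". The caption of the pain flowchart (Figure 1) gives the question "Can you quantify your pain between 0 and 10" and adds a behavioural scale; it also defines which patients count as not cooperative.

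**The concern.** Headache, dizziness and nausea exist as the patient's report. An examiner may see vomiting or unsteadiness, but most cases leave nothing to find, and severity cannot be graded by looking. The method named in Table 1 therefore does not fit three of the four effects it is meant to detect. The patients make this worse: with a tracheotomy and a ventilator they cannot easily speak, so a symptom that nobody asks about may go unrecorded.

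The trial's stated objective is efficacy and safety, and these effects are the ones described to families at consent. The safety analysis is the between-group difference in adverse events. If symptoms are missed at the same rate in both arms, the counts fall and the absolute difference moves toward zero, which is the direction that makes a drug look safe.

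**Working it through.** **Method against outcome.** The plan states no figure for this outcome, so there is none to reproduce. The check is whether each subjective state has a method that can detect it:

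| State | Method in the article | Patient asked? |
|---|---|---|
| Sleep quality (RCSQ) | Five 100 mm scales, with assisted marking | Yes |
| Anxiety (VAS-A) | 100 mm scale | Yes |
| Pain | 0 to 10 rating; a behavioural scale is also given | Yes, where cooperative |
| Headache, dizziness, nausea | Daily physical examination | Not stated |

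The side-effect symptoms are the exception. The first three rows show that the trial expects patients of this kind to be able to answer questions.

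**Direction.** 'Randomization with double-blind and allocation concealment' blinds all study personnel except the pharmacist. The chance of missing a symptom should therefore be about equal in the two arms. With detection probability *s* (sensitivity) and no false positives:

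- recorded rate = *s* × true rate, in each arm
- recorded risk difference = *s* × true risk difference
- recorded relative risk = true relative risk

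The relative risk is preserved on average, but it rests on fewer events. The absolute difference and the incidence itself are too low.

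**Illustration.** The documents give neither event rates nor *s*, so both are assumptions. The 99 per arm is the planned recruitment. With recorded rates p₁ and p₂ and their mean p̄:

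power = Φ{ [ |p₂ − p₁| − 1.96 √(2p̄(1 − p̄)/99) ] / √([p₁(1 − p₁) + p₂(1 − p₂)]/99) }

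Example with 20% v 10% and *s* = 1: (0.10 − 1.96 × 0.05075)/0.05025 = 0.01, so power is about 50%.

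| Assumed true rates | *s* | Recorded rates | Risk difference (points) | Power |
|---|---|---|---|---|
| 20% v 10% | 1.0 | 20% v 10% | 10 | about 50% |
| | 0.8 | 16% v 8% | 8 | about 41% |
| | 0.5 | 10% v 5% | 5 | about 27% |
| | 0.3 | 6% v 3% | 3 | about 17% |
| 10% v 5% | 1.0 | 10% v 5% | 5 | about 27% |
| | 0.8 | 8% v 4% | 4 | about 22% |
| | 0.5 | 5% v 2.5% | 2.5 | about 15% |
| | 0.3 | 3% v 1.5% | 1.5 | about 11% |

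The harm signal weakens steadily as detection falls, but it does not vanish. Power is also modest with perfect detection, so poor ascertainment adds to a limit that the sample size already sets.

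**The case against.** The strongest reply is that a table cell in a condensed article may be shorthand for a daily bedside assessment, during which an intensivist would naturally ask how the patient feels. Nothing in the article forbids questions, and the patients are awake enough to answer. This stands in part. It is why under-counting is probable rather than certain, and why a reader should not infer that the outcome cannot measure what it names. It does not remove the point, because the article names a method, and the named method is the wrong kind for these symptoms.

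A second reply is that this is one of eleven secondary outcomes, and that severe adverse events, daily vital signs, laboratory values and mortality are also recorded. That is true and limits the importance. Those data do not, however, capture headache, dizziness or nausea.

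A reader might also infer that drowsiness is wrongly defined, because a sleeping patient could be counted as having a side effect. The documents do not support that as a finding. No text says that a sleeping patient is recorded as drowsy, and a time window or scale is detail that an article commonly leaves to the full protocol. Nor would a cut-off of RASS −1 or below settle it. The caption of the agitation flowchart (Figure 2) places RASS 0/−1 within the target of an awake and tranquil patient. The Background puts about half of ICU sleep in the daytime, so a daytime score could still catch sleep.

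**Conclusion.** The point holds for headache, dizziness and nausea. As written, the ascertainment method does not fit these symptoms, and it differs from the self-report that the protocol uses for sleep, anxiety and pain. The probable result is under-counting in both arms and a smaller absolute difference, so low or similar rates would not show that melatonin is safe.

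This rests on two assumptions: that the row is applied literally, and that blinding keeps detection similar in the two arms. The size cannot be derived from the documents, and the figures in the table only show how the dilution works. The effect is confined to a secondary outcome and leaves the primary outcome and its analysis untouched.

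**What to change.** Amend the side-effects row of Table 1. Once a day through the treatment period, the blinded intensivist or daily assessor asks each patient who can communicate about headache, dizziness and nausea, and records a severity rating for each. The assisted communication already in place for the RCSQ and VAS-A can be used. Doses are given at 9:00 pm on days 2 to 5, so the questioning should run to day 6 if it is to cover the last dose. A patient who cannot communicate should be recorded as not assessable, not as symptom-free.

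The cost is a few questions per patient per day and somewhat higher recorded rates in both arms. If the intensivists already ask, only the text needs correcting. The 'Trial status' section says the study has started, so if the method changes during enrolment, the report should give the date and show side-effect counts before and after it.

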## Background

Sleep deprivation is a major concern in critically ill patients in intensive care units (ICU). Several studies have shown that poor sleep quality and the inability to sleep are the second largest stressors and rank among the top three major sources of anxiety during ICU stays
[1–3]. Sleep for ICU patients is characterised by frequent disruptions, loss of circadian rhythms and a paucity of time spent in restorative sleep stages. Typical findings described by polysomnography (PSG), the gold standard of assessing sleep quality, include increased latency, a higher proportion of non-rapid eye movement (NREM) sleep stage 1 and 2 (or light sleep), and reduced restorative slow wave (SW) and rapid eye movement (REM) sleep, largely because of frequent waking. Although ICU patients may experience normal or near normal total sleep time (TST), approximately 50% of this sleep occurs during the daytime
[4, 5]. In a recent observational study by Elliot *et al.* a 24-hour PSG was used to evaluate the sleep quality in ICU patients
[5]. They found that despite improvements in ICU design, technology and healthcare personnel training, there has been no improvement in the ICU sleep problem
[5–7]. It has been found that there are many extrinsic and intrinsic factors of sleep deprivation in the ICU setting including noise, light, nursing procedures, the presence of existing diseases, inflammatory mediators, anxiety, pain, sedative and opioid medications and mechanical ventilator setting
[8–12]. Furthermore, the occurrence of ICU sleep deprivation is associated with detrimental outcomes, including delirium, difficulty weaning, increased nosocomial infections, prolonged ICU length of stay (LOS) and increased ICU mortality
[13].

Conversely, despite the poor sleep quality that disturbs almost all ICU patients, clinicians remain reluctant to administer traditional sedative-hypnotic drugs in patients with sleep disorders. The major concerns are the side effects of these drugs, mainly that they destroy the structure of sleep, reduce the clinician’s ability to monitor the level of consciousness, induce respiratory depression and lower blood pressure
[14].

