[31]. Most importantly, although melatonin has hypnotic, sedative and analgesic properties, it has few respiratory and hemodynamic effects.

The interest in melatonin as a potential therapeutic or prophylactic agent in the management of sleep disturbance in the ICU derives from the demonstrated low plasma concentrations and altered secretion patterns of melatonin in critically ill patients. Shilo *et al*. studied the day secretions of melatonin in a group of ICU patients compared to a group of patients in ordinary medical wards. They found that the nocturnal peak of melatonin was missing in most ICU patients
[32]. Mundigler *et al*. described a disturbed pattern of circadian secretion of melatonin in ICU patients with sepsis (16 out of 17 patients) but a preserved circadian rhythm in ICU patients who did not have sepsis (six out of seven patients)
[33]. Olofsson *et al*. found that the circadian rhythm of melatonin secretion was abolished in mechanically ventilated patients in the ICU
[34]. Perras *et al*. suggested that the nocturnal melatonin concentrations in ICU patients were negatively correlated with illness severity
[19]. In addition, various drugs commonly used in the ICU have been reported to alter melatonin secretion and to decrease the plasma levels of melatonin
[35] including benzodiazepines, non-steroidal anti-inflammatory drugs (NSAIDs), corticosteroids and beta-blockers. Therefore, low melatonin levels, poor sleep quality and illness have a reciprocal causation interaction and form a vicious circle. The supplementation of exogenous melatonin to remodel the melatonin level in the human body that approaches the physiological state might be one of most effective strategies for improving sleep.

Both melatonin and cortisol are biological markers of the circadian rhythm. Some previous studies have shown that there is a hypo-secretion of melatonin and an overall high cortisol excretion in most patients in the ICU. Cortisol is an important stress hormone that would be invoked by the noise, light and other stressors in the ICU and leads to anxiety and sleep disturbance. It is known that melatonin can reduce the adrenocortical response to stress and down-regulate the synthesis and release of cortisol. Moreover, in addition to reducing the stress, the role of melatonin as an antioxidant and anti-inflammatory agent or part of sepsis treatment is widely discussed. Thus, administration of melatonin might significantly benefit ICU patients.

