## Methods/Design

### Study design and outcomes

The present study is a prospective, single-centre, randomized, double-blind, placebo-controlled, two-arm trial in patients with sleep deprivation in the ICU. All eligible patients in the ICU will be 1:1 randomized to the treatment intervention with melatonin or placebo. The objective of the trial is to evaluate the efficacy and safety of melatonin for ICU sleep deprivation. The definitions of the variables in the objectives are reported in Table 
1.

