### Statistical analysis

All analyses will be performed according to the intention-to-treat principle, that is, all randomized patients will be analysed in the groups to which they were originally allocated and will be blinded to treatment assignment. Baseline patient characteristics will be compared and described using the appropriate statistics. Categorical variables will be presented as the numbers and percentages and will be analyzed by the *χ*^2^- tests or Fisher’s exact tests, or when appropriate, as relative risks. Continuous variables will be checked for normal distribution by the Kolmogorov-Smirnov test. Normally distributed variables will be expressed by their mean and standard deviation; non-normally distributed variables will be expressed by their medians and 95% confidence levels. Comparisons of continuous variables will be performed using Student’s *t*-test for normally distributed variables and the Mann-Whitney U test for non-normally distributed variables. Appropriate (linear, logistic, or Poisson) regression will be generated for the identification of the determinants of outcomes and for the correction of baseline covariates.

One-way repeated measures analysis of variance (ANOVA) were used to determine differences in the sleep variables, the subjective sleep quality, anxiety levels and plasma levels of melatonin, cortisol and norepinephrine. Twenty-eight day mortality will be analysed according to the Kaplan-Meier method and the results will be compared with the log-rank test hazard ratios and reported with 95% confidence limits. The number of delirium-free days, ventilation-free days and antibiotics-free days will be tested by Student’s *t*-test for normally distributed data and the Mann-Whitney U-test for non-normally distributed data. The differences in adverse events between the intervention and placebo groups are used for safety analyses. All tests of significance will be at the 5% significance level and two-sided. All of the data in this trial will be assessed with SPSS Statistics version 20.0 (SPSS, Chicago, Illinois, United States). The main analysis will be fully specified before unmasking.

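### The Table 1 side-effect definition omits the breathing, blood-pressure and (drowsiness aside) consciousness measures on which the safety rationale rests, although the trial records them daily

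*Protocol article*

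**What the plan says.** Under Study design and outcomes, the protocol article states: "The objective of the trial is to evaluate the efficacy and safety of melatonin for ICU sleep deprivation". It refers the reader to Table 1 for the definitions of the variables involved. The safety entry there is the side-effects row: "Headache, dizziness, nausea, and drowsiness, determined daily by physical examination by the intensivist, and withdrawal symptoms upon discontinuation evaluated after the drugs are stopped". The matching secondary outcome is "k) the incidence and severity of melatonin side effects in ICU patients".

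The safety rationale is in the Background. Clinicians are described as reluctant to use conventional hypnotics because, besides disturbing sleep structure, these drugs "reduce the clinician’s ability to monitor the level of consciousness, induce respiratory depression and lower blood pressure". Melatonin is set against them: "although melatonin has hypnotic, sedative and analgesic properties, it has few respiratory and hemodynamic effects". Under Ethical aspects and informed consent, families are to be told that the product gives good sleep with no respiratory depression.

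Data collection and management calls for "daily information including the vital signs and lab parameters, the SOFA score, neurological monitoring (RASS, CAM-ICU, and GCS", together with ventilation mode, parameters and duration. The same section lists vital signs as temperature, blood pressure, heart rate and respiratory rate.

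The only sentence on safety under Statistical analysis is: "The differences in adverse events between the intervention and placebo groups are used for safety analyses".

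**The concern.** The claimed advantage over other sleep drugs lies in breathing, blood pressure and consciousness. The population makes these domains important: patients have acute respiratory failure, are mechanically ventilated and are ready to be weaned. Yet the side-effects row holds the four symptoms that the Background cites from a meta-analysis as the most common with melatonin, plus withdrawal symptoms. Of the three domains in the rationale, it touches only consciousness, through drowsiness.

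At stake is how far the safety conclusion can reach. The Abstract hopes to be able to recommend a treatment that is safe. A report that follows Table 1 could describe headache, dizziness, nausea and drowsiness by arm and leave the reader unsure whether the respiratory and haemodynamic part of the argument had been examined. The data needed to examine it would already be in the database.

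**Working it through.** The documents give no safety figure to reproduce, so the main check sets the sections side by side.

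| Domain in the rationale | In the Table 1 side-effects row? | Recorded daily? | Between-arm comparison named? |
|---|---|---|---|
| Breathing | No | Yes: respiratory rate; ventilation mode and parameters | None for respiratory rate. Ventilator-free days to day 28 are compared (indirect) |
| Blood pressure | No | Yes: blood pressure | None |
| Consciousness | Drowsiness only | Yes: RASS, GCS, CAM-ICU | None for RASS or GCS. Delirium-free days at 8 and 28 days are compared (indirect) |

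**Is Table 1 the governing definition?** Study design and outcomes says that it defines the variables in the objectives. The row is therefore a stated definition, not a detail deferred to another document.

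**Does the analysis section widen it?** Possibly. The safety sentence refers to adverse events, which the article neither defines nor limits to the Table 1 list. End of participation in the study also uses a wider idea, since a severe adverse event or a worsening condition ends participation. A recognised respiratory or hypotensive event could be counted on this reading. The article does not say whether it would be.

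**Which analyses are named?** Tests or models are specified for sleep variables, subjective sleep quality, anxiety, melatonin, cortisol and norepinephrine, 28-day mortality and the three free-day outcomes. Respiratory rate, blood pressure, RASS and GCS are not among them.

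**Context figures.** These use three assumed numbers of patients per arm: 79 (99 × 0.8 = 79.2), the 82 of the sample-size section, and all 99 randomised.

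- Zero events among n treated patients, one-sided 95% upper bound = 1 − 0.05^(1/n):
  - n = 79: 3.7%
  - n = 82: 3.6%
  - n = 99: 3.0%
- Standardised mean difference detectable with 80% power at two-sided 5% ≈ (1.96 + 0.84) × √(2/n):
  - n = 79: 2.80 × 0.159 = 0.45 (0.449 with the t distribution)
  - n = 99: 2.80 × 0.142 = 0.40

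The first figure bounds an event rate and the second is a shift in a group mean, so they cannot be set against each other. They show only that a count of events and a comparison of measured values give different information at this sample size. They do not show that a harm would be missed.

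**The case against.** The strongest case against the point has four parts.

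1. **The analysis is wider than Table 1.** Adverse events are compared without restriction, drowsiness bears on consciousness, and ventilator-free days, delirium-free days and mortality are all compared between arms. This stands, and it rules out a stronger reading that a reader might infer: that breathing, blood pressure and consciousness are never compared. The free-day and mortality outcomes are still indirect. They run up to day 28 and have many causes, so they do not isolate physiology over four nights of dosing.

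2. **Ascertainment is active.** A reader might infer that safety relies on spontaneous reports. The text does not support that: Table 1 has the intensivist determine side effects by daily examination, and staff have daily vital signs, RASS and GCS from which to recognise an event. This stands. However, the examination is described only for the listed symptoms, so how other events are identified is not stated.

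3. **A general rule could apply.** The Statistical analysis section says continuous variables are compared by t-test or Mann-Whitney test, without naming variables. Nothing prevents its use for the daily measures, but nothing commits the trial to it. It also makes no provision for repeated readings or a pre-dose adjustment.

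4. **This is a condensed article.** Adverse-event definitions and vital-sign tables are commonly left to the full protocol or analysis plan, and their absence alone would be no finding. This carries weight and limits the point to what is printed: a definition narrower than the rationale it serves, and two safety terms that are not linked.

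Interpretation is also difficult. Respiratory rate in a ventilated patient depends partly on mode and settings, RASS is ordinal, and the clock time of the daily readings is not given. This is a reason for a descriptive comparison with no claim of power.

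**Conclusion.** The point holds in a limited form. The side-effect definition is too narrow for a trial whose objective includes safety and whose safety argument concerns breathing, blood pressure and consciousness. The measures are collected, but no graded between-arm comparison of them is named, and side effects in Table 1 are not tied to adverse events in the Statistical analysis section.

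The documents do not show that these harms would go uncompared or undetected. Nor do they commit the trial to declaring safety from symptom counts, since the Abstract's statement is conditional. The gap has no numerical size, and the context figures rest on assumed numbers per arm.

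The conclusion assumes that any fuller document does not already define adverse events more widely or specify such a comparison, and that daily recording continues to day 6. It is a worthwhile, inexpensive improvement and leaves the efficacy analysis untouched.

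**What to change.** 1. **Reconcile the terms.** State whether the adverse events compared under Statistical analysis are the Table 1 side effects or a wider set. If wider, say how they are identified and make the Table 1 row and secondary outcome (k) agree.

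2. **Add a descriptive safety comparison.** Summarise the recorded respiratory rate, blood pressure, RASS and GCS by arm over days 2 to 6, with estimates and confidence intervals adjusted for the pre-dose value. As dosing starts at 9 pm on day 2, specify which readings are pre-dose. Use an ordinal method for RASS and GCS. Present respiratory rate alongside ventilator mode. Show how many patients contribute each day and why others stopped, because severe adverse events and deterioration end participation. Fix these choices before unmasking.

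3. **Limit the conclusion.** Confine any statement of respiratory or haemodynamic safety to what was compared.

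The cost is a few lines of text and one table. It needs no new measurement, staff or patients and no change to treatment. The downside is a few extra safety comparisons, to be read descriptively.
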